## Abstract

**Introduction:**

Circulating prostaglandin E_2_ levels are elevated in acutely decompensated cirrhosis and have been shown to contribute to immune suppression. Albumin binds to and inactivates this immune-suppressive lipid mediator. Human albumin solution (HAS) could thus be repurposed as an immune-restorative drug in these patients.

This is a phase III randomised controlled trial (RCT) to verify whether targeting a serum albumin level of ≥35 g/L in hospitalised patients with decompensated cirrhosis using repeated intravenous infusions of 20% HAS will reduce incidence of infection, renal dysfunction and mortality for the treatment period (maximum 14 days or discharge if <14 days) compared with standard medical care.

**Methods and analysis:**

Albumin To prevenT Infection in chronic liveR failurE stage 2 is a multicentre, open-label, interventional RCT. Patients with decompensated cirrhosis admitted to the hospital with a serum albumin of <30 g/L are eligible, subject to exclusion criteria. Patients randomised to intravenous HAS will have this administered, according to serum albumin levels, for up to 14 days or discharge. The infusion protocol aims to increase serum albumin to near-normal levels.

The composite primary endpoint is: new infection, renal dysfunction or mortality within the trial treatment period. Secondary endpoints include mortality at up to 6 months, incidence of other organ failures, cost-effectiveness and quality of life outcomes and time to liver transplant. The trial will recruit 866 patients at more than 30 sites across the UK.

**Ethicsanddissemination:**

Research ethics approval was given by the London-Brent research ethics committee (ref: 15/LO/0104). The clinical trials authorisation was issued by the medicines and healthcare products regulatory agency (ref: 20363/0350/001–0001). The trial is registered with the European Medicines Agency (EudraCT 2014-002300-24) and has been adopted by the National Institute for Health Research (ISRCTN 14174793). This manuscript refers to version 6.0 of the protocol. Results will be disseminated through peer-reviewed journals and international conferences. Recruitment of the first participant occurred on 25 January 2016.

Strengths and limitations of this studyThis is the first prospective, interventional randomised controlled trial with the primary aim of assessing the effects of serum albumin targeted 20% human albumin solution (HAS) infusions on infection, organ failure and death in hospitalised patients with decompensation of liver cirrhosis.Study design was optimised by a prior 80-patient feasibility study.Cost-effectiveness and quality of life assessment will review whether any outcomes are sustainable and feasible in a national health service setting.The study is unblinded to site investigators due to lack of agreement regarding the control infusion fluid and high cost required.Patients in the control arm may receive 20% HAS as part of current international guidance as it would be unethical to withhold this in certain situations.

## Introduction

Liver disease is an increasing cause of mortality currently in the UK and is the fifth most common cause of death.^1^ These deaths are predicted to double over the next 20 years^2^. Mortality is mainly seen in the middle-aged group. Liver disease has surpassed lung and breast cancers as the leading causes of years of working life lost, and are set to overtake ischaemic heart disease within 2–3 years^3^.

Patients with complications of liver failure secondary to liver cirrhosis are described as decompensated patients. They are highly prone to bacterial infection^4^ secondary to immune dysfunction,^5^ with nosocomial (hospital-acquired) infection rates of 35% compared with 5% in non-cirrhotic patients.^6 7^ Of those who develop infection with organ dysfunction, 60%–95% will die, often following prolonged intensive care unit (ICU) admission.^8^ There is, however, no medical strategy to restore immune competence.

It has been demonstrated that elevated circulating prostaglandin E_2_ (PGE_2_) levels contribute to immune suppression in acutely decompensated patients.^9^ The plasma protein albumin binds and catalyses the inactivation of PGE_2_.^10^ The binding capacity of endogenous albumin is known to be defective in cirrhosis^11 12^ and improves following albumin infusions.^13^ Albumin is synthesised in the liver and levels fall as the synthetic function of the liver declines in advanced cirrhosis. Therefore, low albumin levels, with defective binding function, make PGE_2_ more bioavailable. We found a serum albumin of <30 g/L predicted plasma-induced macrophage dysfunction in a small cohort of decompensated cirrhosis patients^9^ and this was reversed when albumin levels were increased to ≥30 g/L. This finding has recently been validated in a multicentre clinical trial^13^; however, it is not known if these ex vivo observations translate into an improvement in clinical outcomes.

We propose a novel strategy to repurpose 20% human albumin solution (HAS) as an immune-restorative drug in patients with decompensated liver cirrhosis with the aim of maintaining serum albumin at near-normal levels.

The Albumin To prevenT Infection in chronic liveR failurE (ATTIRE) phase II single-arm, multicentre feasibility trial^14^ (n=80) verified that daily intravenous human albumin infusions restored serum albumin levels to near normal in hospitalised patients with decompensated cirrhosis, that it was safe and that there was physician equipoise prior to proceeding to a large randomised controlled trial (RCT).^15^ It has also allowed refinement of our definitions of RCT outcomes.

This phase III RCT (n=866) will assess the impact of 20% HAS treatment on the incidence of nosocomial infections, organ dysfunction and mortality in patients admitted to hospital with decompensation of liver cirrhosis.

## Methods and analysis

### Primary objective

To verify whether raising and maintaining serum albumin levels ≥30 g/L in patients admitted with decompensated cirrhosis using repeated 20% HAS infusions will reduce incidence of infection, renal dysfunction and mortality for the treatment period (maximum 14 days or discharge if <14 days) compared with standard medical care (figure 1). To raise and maintain serum albumin levels above 30 g/L, 20% HAS will be prescribed and administered in the intervention arm if levels are below 35 g/L.

**Figure 1 F1:**
[figure not shown]
Overview of Albumin To prevenT Infection in chronic liveR failurE (ATTIRE) randomised controlled trial (RCT) study protocol. HAS, human albumin solution; HRS, hepatorenal syndrome; LVP, large volume paracentesis; QOL, quality of life; SBP, spontaneous bacterial peritonitis.

Secondary objectives are to assess the impact of the intervention on development of other organ dysfunction (cardiac, respiratory, brain and liver), cost-effectiveness, quality of life (QOL) and sustainability of any outcomes over a 6-month follow-up period.

### Trial design

This is a multicentre, open-label, RCT in which patients will either be treated with 20% HAS to raise and maintain serum albumin above 30 g/L or continue to receive their usual standard of care treatment. Eight hundred sixty-six sequential patients admitted to 30 UK participating hospitals with a clinical diagnosis of cirrhosis and decompensation will be screened using the inclusion and exclusion criteria (table 1). Decompensation includes: jaundice, ascites, hepatic encephalopathy, variceal bleeding, coagulopathy and hepatorenal syndrome (HRS).

**Table 1 T1:** Patient selection criteria

Patient inclusion criteria	Patient exclusion criteria
All patients admitted to hospital with acute onset or worsening of complications of cirrhosis	Advanced hepatocellular carcinoma with life expectancy of less than 8 weeks
Over 18 years of age	Patients who will receive palliative treatment only during their hospital admission
Predicted hospital admission ≥5 days at trial enrolment, which must be within 72 hours of admission	Patients who are pregnant
Serum albumin <30 g/L at screening	Known or suspected severe cardiac dysfunction
Documented informed consent to participate (or consent given by a legal representative)	Any clinical condition which the investigator considers would make the patient unsuitable for the trial
	The patient has been involved in a clinical trial of investigational medicinal products (IMPs) within the previous 30 days that would impact on their participation in this study
	Trial investigators unable to identify the patient (by NHS number)

NHS, National Health Service.

As advanced liver disease requires frequent hospital readmissions, patients may be enrolled in the RCT more than once, with a 30-day ‘washout period’ following discharge after the first enrolment, during which time they cannot be enrolled for a second time. This is to account for albumin’s half-life of 18–21 days^16^. Patients re-entering the trial in this way will be rerandomised, so that each enrolment will be considered as an independent patient ‘presentation’.^17^

To ensure homogeneity in the approach to patient recruitment, intervention and data collection, all sites received introduction training and regular follow-up re-training plus monitoring and support visits from the sponsor.

### Clinical trial endpoints

#### Primary endpoint

A composite endpoint comprising incidence of infection, renal dysfunction and mortality within the treatment period (for a maximum of 14 days OR when the patient is considered fit for discharge if <14 days).

The three components of the composite endpoint are:New infection: indicated by clinician diagnosis and clinical evidence provided on completed infection case report form (CRF). Blinded data from a clinically representative sample of patients will be scrutinised for the presence of infection by a clinical trial endpoint review committee. The committee will contain microbiologists who will validate the presence of infection according to peer reviewed criteria^18^ (see online supplementary appendix 1).Renal dysfunction: a serum creatinine increase of ≥50% as compared with serum creatinine at randomisation OR the patient is initiated on renal replacement support (either haemodialysis or haemofiltration) OR a rise in serum creatinine of ≥26.5 μmol/L within 48 hours.Mortality
10.1136/bmjopen-2018-023754.supp1Supplementary file 1

Primary endpoint data will be recorded throughout the treatment period; however, only contributing events captured on the treatment day 3 CRF through to the day 15 CRF (the end of treatment examination day) will contribute to the primary outcome. This allows the biological effect of albumin to be established at least 24 hours following initiation of treatment.

If the participant is discharged or deemed medically fit for discharge prior to day 15, no further primary outcome data will be measured after this date, as this will signal the end of the participant’s treatment period.

#### Secondary endpoints

Mortality at 28 days postrandomisation and at 3 and 6 months postdischargeTime to outcome (first event of infection/renal dysfunction/death)Incidence of respiratory, circulatory and cerebral dysfunction during the treatment period (based on modified components of the Chronic liver failure-sequential organ failure assessment (CLIF-SOFA)^19^ score).Incidence of liver transplant within 6 months of treatmentTotal amount of HAS administered during the treatment periodDuration of hospital stayChange in prognostic score (assessed by Model for End Stage Liver Disease (MELD)) between randomisation and end of treatment period.Days in ICU during treatment periodIncremental cost and cost-effectiveness up to 6 months postdischargeImpact on QOL up to 6 months postdischargeSafety and tolerability of HAS as indicated by serious adverse eventsUse of terlipressin for (1) renal dysfunction, (2) hypotension and (3) variceal bleeding.

Patients in the RCT will be followed up 3 and 6 months (+/−1 month) following discharge from hospital. Exploratory objectives are listed in online supplementary appendix 2.

10.1136/bmjopen-2018-023754.supp2Supplementary file 2

### Patient population

This will include all patients admitted to hospital with complications of decompensated liver cirrhosis and serum albumin <30 g/L, aged over 18 years with anticipated hospital length of stay of 5 or more days at trial enrolment, which should be no later than 72 hours from admission. This is subject to exclusion criteria as detailed in table 1. The diagnosis of cirrhosis will be made by the clinical team as per standard UK practice and does not require liver biopsy or imaging. Acute decompensation of liver cirrhosis associated with organ failures is termed ACLF (acute on chronic liver failure). ACLF has a number of definitions^20 21^ based on the SOFA score, all are associated with a poor prognosis. This study will include patients with decompensated cirrhosis with and without ACLF; it will also record the development of ACLF during the study treatment period.

### Consent

Patient information sheets (see online supplementary appendix 3) will be given to and discussed with potential patients before consent is sought. Informed consent will be obtained from each participant or his or her legal representative. Patients who lack mental capacity, for any reason, are not excluded from the trial. An important subgroup of patients will have hepatic encephalopathy and these patients may lack capacity to consent; however, these patients may be among those that receive maximum benefit from the intervention.^21–23^ In this case, consent will be sought from an appropriate legal representative independent of the research team as per current UK clinical trials regulations.^24^

10.1136/bmjopen-2018-023754.supp3Supplementary file 3

### Intervention

After randomisation (when serum albumin is <30 g/L) patients will receive either daily dose of 20% HAS intravenously if their serum albumin level is less than 35 g/L (at approximately 100 mL/hour) or standard medical care (which may include 20% HAS infusions for indications listed in established guidelines only; see below) for a maximum of 14 days or discharge (if <14 days). The volume of HAS each day will be determined by the patient’s serum albumin level on that day (or the closest previous measurement if there are no results from that day available).

Table 2 shows the suggested dosing protocol for albumin administration in the treatment arm group. This is a suggested regimen and responsible clinicians are given flexibility to alter this depending on the clinical situation. The effectiveness of this protocol, and approach, was verified in the ATTIRE feasibility study.^15^ Differing regimens may be used to cover large volume paracentesis (LVP) (8 g of albumin per litre of ascites drained) or treat HRS (1 g of albumin per kilogram of body weight) as per international guidelines^25 26^ but HAS *must* be prescribed and given if serum albumin <35 g/L unless there are any safety concerns. All variations will be recorded in the patient’s daily CRF.

**Table 2 T2:** Treatment arm dosing protocol for 20% human albumin solution (HAS) administration (amounts per day) as advised by measured serum albumin level on that day

Patient’s serum albumin level	Amount of 20% HAS to be administered
≥35 g/L	none
30–34 g/L	100 mL
26–29 g/L	200 mL
20–25 g/L	300 mL
<20 g/L	400 mL

Twenty per cent HAS will only be given in the standard of care arm if the patient requires large volume paracentesis or has spontaneous bacterial peritonitis (SBP) or HRS (as per established guidelines^26–28^). This needs to be clearly recorded in the patient’s CRF, and if HAS is given for any other indication in the Standard of Care arm, this will be considered a protocol deviation. The administration of HAS in the Standard of Care arm will be closely monitored by the Independent Data Monitoring Committee (IDMC).

Randomisation will use a minimisation algorithm incorporating a random element, stratifying by centre, MELD score, and number of organ dysfunctions, serum albumin level and if antibiotics are currently being prescribed. To ensure maximum balance is achieved across the stratification factors, minimisation will be carried out on these factors separately.

### Evaluations during and after treatment

Clinical, biochemical, microbiological, health economic and QOL data will be collected during the trial treatment period (see online supplementary appendix 4) using information from hospital notes that is recorded as standard of care. There is follow-up at 3 and 6 months. The blood, urine and stool samples collected for immune function tests will be analysed in a blinded fashion at a central site.

10.1136/bmjopen-2018-023754.supp4Supplementary file 4

### Patient and public involvement

Patients who have had a previous diagnosis of liver cirrhosis were involved in the development of the research question and outcome measures. Patient feedback led to the addition of QOL evaluation. The study protocol and patient information leaflets were reviewed by our patient representatives with positive feedback. In addition, an independent patient representative sat on the ethics approval panel. Results will be disseminated to patients via open access publication and our local trials teams.

### Statistical considerations

#### Sample size

A 30% incidence of nosocomial infection in acute decompensated cirrhosis patients is well documented with up to 30% of these patients developing organ dysfunction^21 29^ and an overall mortality of 38% at 1 month.^18^
^21 29^ These figures are supportive of 30% as a conservative estimate for the composite primary endpoint of incidence of new infection, renal dysfunction or mortality up to 14 days from randomisation.

We have assumed that the ‘immune-restorative’ albumin treatment would reduce this rate by 30% to a rate of 21%, which would be considered clinically relevant. Three hundred eighty-nine patients per arm would be sufficient to detect such a difference with 80% power at a significance level of 0.05. Allowing for loss to follow-up/withdrawal of 10% from the trial, we will aim to recruit 433 to each arm (866 in total).

### Statistical evaluation

A detailed statistical analysis plan will be written and approved by the Trial Steering Committee (TSC) before the substantive analysis of unblinded trial data.

Baseline characteristics will be summarised by treatment using appropriate descriptive statistics, means and SD for approximately normally distributed variables, medians and IQRs for non-normally distributed variables and counts (percentages) for categorical variables.

#### Primary outcome

The primary outcome is the difference in event rates, according to treatment, of the composite endpoint of infection, renal dysfunction and mortality within the intervention period (from ≥24 hours from the start of treatment/randomisation up to a maximum of 14 days or up to discharge if this is prior to 14 days).

Since the primary outcome has a binary classification, logistic regression will be used to determine whether there is any difference in rates due to treatment, by inclusion of a binary covariate indicating treatment. The results will be adjusted for predetermined prognostic factors used as stratifying variables in the randomisation, which shall be included as additional covariates in the model. The model coefficient due to treatment will give an estimate of the difference in log odds, or equivalently (exponentiated to give) an estimate of the odds multiplier, that is, the change in odds of a negative outcome on the composite endpoint due to treatment with albumin. It is expected that this effect will be negative, so that treatment with albumin is seen to reduce the odds of a negative outcome. A reduction from 30% to 21% would be associated with a reduction in odds of around 38%. Predicted probabilities will be presented for the composite outcome for each of the treatment arms, adjusted for the model covariates.

The effect of treatment on the individual components, infection, renal dysfunction and mortality will be reported separately.

#### Secondary and exploratory outcomes

Secondary and exploratory outcomes will be handled similarly. Continuous secondary outcome measures will be analysed using a linear regression model, and time-to-event outcomes using Kaplan-Meier plots and Cox’s proportional hazards models where covariate adjustment is necessary.

All statistical tests will use a two-sided p value of 0.05, unless otherwise specified, and all CIs presented will be 95% and two-sided. All statistical analyses will be performed using Stata (StataCorp, College Station, Texas, USA).

### Economic evaluation

The economic evaluation will consist of two parts. The primary analysis will be a decision analytic model comparing the expected lifetime costs and benefits of treatment reported in terms of the cost per incremental quality-adjusted life-years (QALYs) gained. QALYs will be calculated based on the health-related QOL (HRQL) and mortality data collected during the trial. HRQL will be measured according to the 5 level EQ-5D (EQ-5D-5L) (www.euroqol.org), which we will collect at baseline, discharge, 3 months and 6 months (+/–1 month) for each individual patient. If patients are rerandomised, they will have separate follow-up events for each episode of rerandomisation, unless the patient is rerandomised within the follow-up phase of the study. Utility scores will be calculated using UK-specific tariffs and adjusting for baseline differences in patients in the trial arms if necessary. These will be extrapolated over the expected lifetime of the patient and where necessary will draw on the existing literature. The final form of the decision analytic model will be determined during the trial period. Appropriate methods for estimating changes in health over time, such as state-transition models, will be given consideration.

The secondary economic analysis will be a ‘within-trial’ analysis, reporting on the incremental cost and benefits observed during the trial period and follow-up periods. The cost-effectiveness measures in the within-trial analysis will be the incremental cost per infection avoided and the incremental cost per QALY gained. Costs will be measured as described below. Infections avoided will be derived from the primary outcome in the trial.

Patient resource use will be assessed using hospital patient records and a self-complete resource use form, the client services receipt inventory (CSRI). The volume of resource use for each cost component will be measured directly in the trial from patient records and using the CSRI. A detailed economic evaluation analysis plan will be developed for approval by the TSC.

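### The 3- and 6-month mortality time points, and the end of the cost and QALY window, are set from discharge instead of randomisation, so follow-up length depends on hospital stay

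*Protocol article*

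**What the plan says.** Protocol article, Secondary endpoints: mortality is listed at 28 days after randomisation and then at 3 and 6 months after discharge. Incremental cost, cost-effectiveness and quality of life are each reported up to 6 months after discharge. Duration of hospital stay is a separate secondary endpoint. On visits, the section says "Patients in the RCT will be followed up 3 and 6 months (+/−1 month) following discharge from hospital".

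Protocol article, Economic evaluation: the EQ-5D-5L is a measure "which we will collect at baseline, discharge, 3 months and 6 months", and "QALYs will be calculated based on the health-related QOL (HRQL) and mortality data collected during the trial". The secondary, within-trial analysis is described as "reporting on the incremental cost and benefits observed during the trial period and follow-up periods". The main economic analysis is different in kind: "The primary analysis will be a decision analytic model comparing the expected lifetime costs and benefits of treatment".

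No section gives a fixed horizon from randomisation for 3- or 6-month mortality or for the within-trial economic analysis. None says where the 3- and 6-month points fall for a patient who dies before discharge.

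**The concern.** A randomised comparison is protected when both arms are followed over the same time from randomisation. Discharge is a later event that treatment can move. The trial is open-label, the albumin arm receives inpatient infusions for up to 14 days or until discharge, and clinicians who know the allocation decide when the patient leaves. If mean stay differs between the arms, so does the time at risk behind the 6-month figures. The arm with the longer stay is credited with more days of life, more QALYs and more cost, and also with more deaths, simply because it is watched for longer.

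The second difficulty is death before discharge. The Sample size section cites "an overall mortality of 38% at 1 month" in this population. The article does not say how many of those deaths occur in hospital, but mortality during the inpatient treatment period is part of the primary endpoint, so some are expected. For these patients a time point counted from discharge has no date.

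**Working it through.** **The plan's own figures.** The article gives no figure for the 3- and 6-month outcomes. Its one calculation, for the primary endpoint (30% versus 21%, 80% power, two-sided 0.05), reproduces with the continuity correction: 389 per arm, 389/0.90 = 432.2, rounded up to 433, and 866 in total. The present point does not touch it.

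**The clocks side by side (Secondary endpoints; Economic evaluation).**
- 28-day mortality: starts at randomisation, ends at day 28.
- 3- and 6-month mortality: time point set from discharge.
- Costs and QALYs: start at baseline, end 6 months after discharge.

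**Horizon from randomisation.** Length = 6 × 30.44 days + days from randomisation to discharge. The article gives no stays, so these are assumed:
- 5 days: 182.6 + 5 = 187.6
- 14 days: 196.6
- 28 days: 210.6
- 60 days: 242.6

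Each extra day in hospital adds one day, before the visit tolerance of 1 month either side.

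**QALY effect of the horizon alone.** Formula: extra days/365.25 × utility × proportion alive. Utility 0.5 and 65% alive are assumptions.
- 1 extra day: 1/365.25 × 0.5 × 0.65 = 0.0009
- 3 extra days: 3/365.25 × 0.5 × 0.65 = 0.0027

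Per survivor, over a wider range:
- 2 days at utility 0.4: 2/365.25 × 0.4 = 0.002
- 10 days at utility 0.8: 10/365.25 × 0.8 = 0.022

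**Mortality effect of the horizon alone.** Assume the same constant hazard h in both arms, so there is no treatment effect, and give every patient in an arm that arm's mean stay. With 6-month mortality m from randomisation, h = −ln(1 − m)/182.6, and mortality at 6 months after discharge is 1 − exp(−h × (182.6 + stay)). All in-hospital deaths are counted. Worked case, m = 40%, stays of 10 versus 15 days: 41.7% versus 42.5%, a difference of 0.8 points. For m from 30% to 50% and stays of 10 versus 12 to 20 days, the spurious difference is 0.3 to 1.8 points at 6 months and 0.3 to 2.5 points at 3 months.

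**Data gap if the horizon is fixed at 180 days.** The earliest permitted last visit is 5 months after discharge: 5 × 30.44 + 5 = 157.2 days for a 5-day stay, and 166.2 for a 14-day stay. The gap to day 180 is therefore about 23 and 14 days.

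**The case against.** The strongest reply is that these are secondary analyses, that post-discharge visits are a sensible schedule, that the bias is small, and that a detailed economic analysis plan is promised. Most of that stands. Nothing in the article shows that stays will differ between the arms. But the discharge origin is stated in the endpoint definitions, so this is not a detail left open. An economic plan with a different horizon would depart from those definitions and would not govern clinical mortality.

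Several stronger readings are tempting, and the article does not support them.

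- *Costs and QALYs have no time origin for in-hospital deaths.* They do: the EQ-5D-5L is collected at baseline and the within-trial analysis includes the trial period. Only the end of the window depends on discharge.
- *Late mortality is confined to discharged patients.* A reader might infer this, and it could reverse the result. Assume in-hospital death of 15% versus 10%, later death of 25% in usual survivors and 60% in the extra 5% who survive. Post-discharge mortality is then 25.0% versus (0.85 × 0.25 + 0.05 × 0.60)/0.90 = 26.9%, while total mortality is 36.3% versus 34.3%. But no such denominator is stated. The Abstract speaks of mortality up to 6 months, and QALYs use mortality data collected during the trial. In-hospital deaths can be counted as deaths, and the reversal then disappears.
- *All these endpoints go into logistic regression.* The sentence "Secondary and exploratory outcomes will be handled similarly" is followed by linear regression for continuous outcomes and by Kaplan-Meier and Cox methods for time-to-event outcomes. The article does not say which group late mortality belongs to.
- *The 1-month visit tolerance biases the comparison.* It applies to both arms alike and is not shown to favour either.

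**Conclusion.** The point holds in a limited form. The 3- and 6-month mortality time points and the end of the cost and QALY window are tied to a post-randomisation event, and no 3- or 6-month date can be set for patients who die before discharge. The comparison may therefore cover unequal time after randomisation.

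The size is modest unless stays differ clearly: about 0.001 to 0.003 QALY for 1 to 3 extra days, and a fraction of a point to under 2 points of 6-month mortality for mean stays 2 to 10 days apart. These figures rest on assumed stays, utilities, survival and hazards, because the article gives none.

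The primary endpoint, 28-day mortality and the sample size are unaffected. The lifetime model is affected only through the trial data that feed it. The change is worth making because it is cheap and removes a dependence on treatment that no later adjustment handles cleanly.

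**What to change.** Keep the visits as scheduled and change only the endpoint definitions.

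- **Mortality:** define the 3- and 6-month endpoints from randomisation, for all randomised presentations, counting in-hospital deaths. Use Kaplan-Meier estimates by arm and the Cox model that the article already plans for time-to-event outcomes, censoring patients lost earlier.
- **Within-trial costs and QALYs:** accumulate over one fixed horizon from randomisation, for example 180 days. Use actual assessment dates, with zero utility and no further cost after death.
- **Wording:** in Secondary endpoints, replace the discharge origin by randomisation for mortality, cost and quality of life. In Economic evaluation, state the horizon.

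This needs rewording and the dates of randomisation, discharge, assessment and death, which a trial of this kind would be expected to record. No visit is added. The downside is that patients seen at the early end of the 6-month window may lack vital status, EQ-5D-5L and resource-use data for up to about three weeks before day 180. The analysis plans should say how that gap is handled: by censoring for mortality (or updating vital status from records), and by interpolation or carrying forward for utilities and costs.
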